**CONTROL ARM**

The control group will receive an information leaflet focusing on key illness perceptions of being at risk of T2DM, developed in the context of Leventhal’s common sense model. The leaflet will also focus on the importance of increasing physical activity and decreasing sedentary behaviour.

**Table 1:** Potential outline of the STAND structured education course which will be delivered to the participants in the intervention arm.

| **Module name** | **Main aims and educator activities** | **Theoretical underpinning** | **Time weighting** |
| --- | --- | --- | --- |
| ***Patient story*** | Give participants a chance to share their knowledge  and perception of sedentary behaviour in relation to diabetes risk and highlight any concerns  they may want addressed in the programme | Common sense model | 10%  (20 min) |
| ***Professional story*** | Use simple non-technical language, analogies, visual  aids and open questions to provide participants with  an overview of healthy glucose metabolism, the  aetiology of diabetes and the risk factors and  complications associated with diabetes  Help participants calculate their own individual  Diabetes risk scores | Common sense model  Dual process theory | 35%  (60 min) |
| ***Diet*** | Give participants an accurate understanding of the  link between diet and metabolic dysfunction | Social cognitive theory  Dual process theory | 15%  (25 min) |
| ***Sedentary behaviour*** | Use simple non-technical language, analogies,  visual aids and open questions to help participants:  identify how reducing sedentary behaviour may improve glucose control and body weight;  understand the current activity recommendations;  explore options for reducing sedentary behaviours in  everyday life; identify barriers to reducing sedentary behaviour; form action  plans and set personal goals  Practical demonstration of how to use the novel exercise technology for the self- regulation of sedentary time. | Social cognitive theory  Behavioural Choice Theory | 40%  (75 min) |

**OUTCOME MEASURES**

All primary and secondary outcome measures will be recorded at 0, 3 and 12 months.

**Primary Outcome:**

The primary outcome is a reduction in sedentary behaviour at 12 months. Sedentary behaviour will be objectively measured using the triaxial Actigraph GT3X model of accelerometer. These accelerometers are the most extensively validated and accurate on the market and they are the only commercially available accelerometers to correlate with energy expenditure as measured by double-labelled water (Plasqui, 2007).

Participants will be asked to wear the accelerometer on a waistband (in the right anterior axillary line) for ten consecutive days during waking hours. A total of 4 days valid wear will be required to count as a valid recording and a ‘valid day’ will consist of at least 10 hours of accelerometer movement data. The accelerometer will record movement data every 5 seconds (i.e., 5 second ‘epoch’). Prolonged periods of no movement, that is, strings of ‘0’, will be assumed to be non-wear time and will be excluded. The primary outcome measure is sedentary time defined as <100 counts per minute (Freedson 1998).

To encourage participants to remember to wear the accelerometer they will be provided with cards to place in convenient locations around the home. We will also send them text messages during data collection periods, reminding them to wear the device.

**Secondary outcomes:**

**Physical activity and body position**

- Accelerometer data
- Inclinometer data
- ActivPAL
- IPAQ questionnaire

Physical activity will be objectively measured using the accelerometer as described above. Secondary outcomes include steps per day, total body movement (counts per day), and time in light-, moderate- and vigorous-intensity physical activity as determined by counts per minute cut points proposed by Freedson et al (1998).

The Actigraph GT3X model incorporates an inclinometer which provides postural data. This has the advantage of allowing the research team to determine subject position (lying or sitting) and periods when the device has been removed.

The ActivPAL is a thigh worn accelerometer which measures the angle of the thigh, providing valuable data on participant posture (ie sitting or lying vs standing). The data obtained from this device will provide invaluable information about the time spent sitting. The ActivPAL will be worn on the thigh for the same 10 day period as the GT3X accelerometer.

The short ‘last-seven-days’ self-administered format of the International Physical Activity Questionnaire (IPAQ) will be used as a self-report measure of activity. This questionnaire provides a comprehensive measure of walking and other moderate- to vigorous-intensity activities carried out for more than 10 continuous minutes at work, in the home, as transport and during leisure time. IPAQ has been shown to have reasonable validity compared to accelerometer data (ρ ~ 0.4) and test-retest reliability (ρ ~ 0.7) in the UK when used as a measure of total moderate- to vigorous-intensity physical activity (Craig 2003). For this study, IPAQ will be used to measure total activity accumulated at work, for transport and in leisure time as well as an overall measure of moderate- to vigorous-intensity physical activity accumulated over all contexts.

### Biochemical variables

- Oral glucose tolerance test
- Blood U&E, lipid profile, liver and thyroid function tests, vitamin D
- Insulin, c-peptide, HbA1c, HOMA-B, HOMA-IR
- hsCRP, TNF alpha, sIL-6, and sIL-6R
- Biomarkers
- Genetics blood sample

Participants will be invited to attend each clinical measurement session after a 12-hour fast and 24 hours of avoiding vigorous intensity exercise.

This study will measure glucose control and insulin sensitivity using: fasting glucose, 2-hour post challenge glucose, fasting insulin, and HbA1c. In addition fasting lipid profile, highly sensitive C-reactive protein, key adipokines (interleukin 6 and its receptors, tumour necrosis factor alpha), urea & electrolytes (sodium, potassium, urea, creatinine) will be measured by venous sampling. This study includes markers of chronic inflammation and adipokines because these variables have been hypothesised to be directly involved in the pathogenesis of type 2 diabetes (Tataranni 2005) and have been shown to be inversely associated with overall physical activity and walking activity (Panagiotakos 2005, Yates 2008). However data on the relationship of these variables with sedentary behaviour is lacking. Therefore this study will further our understanding of the effect of sedentary behaviour change on markers of chronic low-grade inflammation.

In concordance with WHO recommendations those who have a fasting or 2-hour blood glucose level in the diabetes range at any clinical measurement session will be called back for a confirmatory oral glucose tolerance test. If diabetes is confirmed, the participant will be removed from the study and referred to their general practitioner for routine diabetes care.

All venepuncture and OGTT timings will be undertaken by trained phlebotomists who are not part of the scientific advisory team for this study and who are blinded to treatment allocation. All biochemical analyses will also be conducted blinded to treatment group.

Plasma glucose will be measured using a glucose oxidase method on the Beckman Auto Analyzer (Beckman, High Wycombe, UK). Serum cholesterol will be analysed using the cholesterol enzymatic assay (Abbott Clinical Chemistry, IL, USA). High density lipoprotein (HDL) cholesterol will be analysed using the ultra HDL assay (Abbott Clinical Chemistry, IL, USA). Serum triglyceride will be analysed using the triglyceride glycerol phosphate oxidase assay (Abbott Clinical Chemistry, IL, USA). Glucose and lipid profile measurements will be undertaken in the same laboratory located within Leicester Royal Infirmary using stable methodology standardised to external quality assurance reference values.

Plasma IL-6 concentration will be measured as described in detail previously (Robinson et al 2009). Briefly, samples diluted 1:5 were analyzed via sandwich enzyme-linked immunosorbent assays (ELISAs) using commercially available anti-human IL-6 antibody pairs (OptEIA, BD Biosciences, Oxford, UK) and an ELISA amplification system (Invitrogen, Paisley UK). This assay will not distinguish between the soluble and receptor-bound IL-6 and therefore measures total IL-6 content. Absorbance will be read at 490 nm (Spectra Max 190, Molecular Devices, USA) and the concentration of the samples determined by relation to a 4-parameter standard curve and adjusted to take account of the dilution factor of the plasma. The intra assay CV of the assay is 5.7% and has an inter assay CV of 7.2%.

Plasma sIL-6R concentration will be measured as described in detail previously (Robinson 2009). Briefly, samples diluted 1:200 will be analysed via sandwich ELISA using anti-human sIL-6R M182 detection antibody and anti-human sIL-6R M5 biotinylated capture antibody (BD Biosciences, Oxford, UK). Absorbance will be read at 450 nm (Spectra Max 190, Molecular Devices, USA) and the concentration of the samples will be determined by relation to a 4-parameter standard curve and adjusted to take account of the dilution factor of the plasma. The intra assay CV is 3.8% and has an inter assay CV of 5.3%.

TNF-α will be measured using a commercially available ELISA kit (RnD systems, Minneapolis, MN, USA) and high sensitivity CRP will be measured on an automated analyser (Pentra 400, Horiba-ABX, Montpellier, France).

All participants will be sent a results letter highlighting their main clinical results after each measurement session. All participants’ results will be sent to their GP.

In addition to the above biochemical variables, we also collect a blood sample for genetic analysis (informed consent will be obtained before these samples are collected). The aim of this sample will be to investigate the associations and interactions of sedentary behaviour, obesity and genes in the development of T2DM. The genetic assessments will be focused on genes for which there are biological plausibility for interaction. The choice of genes and polymorphisms of interest will be decided by an experienced group of researchers. We will genotype all consenting participants for genetic variants in key genes and analyse the data for gene-lifestyle interaction. The demonstration of differential response to lifestyle change by genotype will not only provide greater aetiological understanding, but will also present the opportunity to investigate possibilities to use genotypic data in risk stratification and identification of individuals who have the potential to benefit most from targeted lifestyle modification.

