**HYPOTHESIS**

The primary hypothesis of the STAND randomised controlled trial is:

- Structured education can decrease sedentary behaviour in young adults at risk of T2DM

The secondary hypothesis is:

- Reduced sedentary behaviour results in favourable changes in key behavioural and biological markers of T2DM risk

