**RANDOMISATION**

Once baseline data have been collected, participants will be randomised to either a control (C) or intervention (I) group, the latter being given the STAND structured education programme aimed at decreasing sedentary behaviour. Randomisation (stratified by age, sex, and ethnicity) will be set up by a statistician.

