**DATA ANALYSIS**

The study will be reported according to the CONSORT statement for randomised control trials. Data will be analysed on an intention-to-treat basis (ITT). Data will be analysed using STATA v10 and SPSS v16 software. Descriptive statistics (mean values and frequencies) will be calculated. Histograms will be used to identify any outliers and to test for normality. Robust ANCOVA modelling will be used to look at the difference between groups in change in continuous outcome measures and logistic regression will be used to analyse categorical variables. Results will be disseminated via peer-reviewed publications and presentations at national and international meetings.

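### Removing randomised participants once diabetes is confirmed conflicts with the intention-to-treat promise and loses 12-month outcomes for anyone confirmed after the 3-month session

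*Protocol*

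**What the plan says.** The protocol's section on biochemical variables states that anyone with a fasting or 2-hour glucose in the diabetes range "at any clinical measurement session will be called back for a confirmatory oral glucose tolerance test". It continues: "If diabetes is confirmed, the participant will be removed from the study and referred to their general practitioner for routine diabetes care".

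Under Outcome measures the timetable is fixed: "All primary and secondary outcome measures will be recorded at 0, 3 and 12 months". Under Randomisation: "Once baseline data have been collected, participants will be randomised to either a control (C) or intervention (I) group".

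The Phase 3 Data analysis section says: "Data will be analysed on an intention-to-treat basis (ITT").

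The glycaemic measures, "fasting glucose, 2-hour post challenge glucose, fasting insulin, and HbA1c", are listed among the secondary outcomes. They serve the secondary hypothesis: "Reduced sedentary behaviour results in favourable changes in key behavioural and biological markers of T2DM risk". The primary outcome is accelerometer-measured sedentary time at 12 months.

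**The concern.** Two of the three measurement sessions come after randomisation, and the removal rule is not limited to the first. A randomised participant can therefore leave the trial because of a value on one of its own outcomes. Intention-to-treat needs outcomes from everyone randomised, as far as they can be obtained. A rule that ends follow-up because of an outcome works against that.

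If the programme lowers glucose, fewer intervention participants than controls should cross the threshold. More controls with poor values would then be lost, the control mean would look better than it is, and a real benefit would be understated. The 12-month primary outcome is lost for the same people. The protocol's background links sedentary behaviour with diabetes, so that loss may not be random either, although nothing in the protocol allows its direction or size to be worked out.

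**Working it through.** **Does the rule reach randomised participants?** Sessions are at 0, 3 and 12 months, and randomisation follows baseline data collection. The rule applies at any session. Removal at 0 months fits the exclusion of diabetes at entry. Removal at 3 or 12 months concerns people already allocated.

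**What is lost, by session?**
- *3 months:* the participant leaves before the 12-month session, so neither the accelerometry nor the 12-month glycaemic measures are taken. The remote follow-up at the end of the study uses national tagging and general practice records and cannot supply accelerometry.
- *12 months:* this is the last scheduled session, and the diabetes-range value exists before the call-back. The text does not say whether it is kept.

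**How many?** The protocol gives no incidence. Assume 1-5% conversion over 12 months, spread evenly, so that 3/12 of cases are detectable by 3 months:
- 178 × 0.01 × 3/12 = 0.4
- 178 × 0.05 × 3/12 = 2.2

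That is 0.25% to 1.25% of those randomised.

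**Effect on the glycaemic comparison.** This was simulated for 2-hour glucose at 12 months with an assumed true difference of -0.50 mmol/l, a removal threshold of 11.1 mmol/l and a correlation of 0.5 to 0.7 between the 3- and 12-month values. All of these inputs are assumptions.

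| Control mean (SD), mmol/l | Removed at 3 months, control v intervention | Estimate after 3-month removal | Estimate if 12-month values are also dropped |
|---|---|---|---|
| 6.0 (1.5) | under 0.1% in each | -0.50 | -0.50 |
| 7.0 (2.0) | 2.0% v 1.1% | about -0.47 | about -0.44 |
| 7.5 (2.5) | 7.5% v 5.1% | -0.42 to -0.45 | about -0.37 |

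Where the estimate moves, it moves towards zero. The middle row removes about (2.0 + 1.1)/2 = 1.55% overall, already above the 1.25% upper figure, for a shift of about 0.03 mmol/l. The simulation uses a single reading with no confirmatory test and does not screen out diabetes at baseline. Both features overstate removal.

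**Effect on the primary outcome's power.** The plan's figure comes first: N per arm = 2 × (1.96 + 0.842)² × 12.1² / 5.67² = 71.5, which rounds up to the stated 72. The stated 89 equals 71.5 × 1.25 = 89.4. After 25% dropout, 89 × 0.75 = 66.75 per arm remain, and power is 77.3%; that shortfall from 80% comes from the dropout inflation and is separate from this point. If diabetes removals come on top of the 25%:
- 1% more removed: 76.8%
- 2% more removed: 76.4%
- 5% more removed: 75.1%

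If the removals fall within the 25%, no further power is lost.

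**The case against.** The strongest reply is that intention-to-treat governs how data are analysed while the removal rule governs participation, and that missing follow-up is commonly handled in an SAP, which is not available here. Part of this stands: the SAP may define the analysis population and the missing-data method. It cannot supply 12-month measurements that the protocol stopped anyone from taking.

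The reply is also right that the scale is probably modest. Participants are aged 18-40 and can enter on BMI alone, the glycaemic outcomes are secondary, and sedentary time is not itself a glycaemic measure. On the other side, people with impaired glucose regulation are admitted, so some conversion is plausible.

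Three stronger readings are tempting, and the protocol does not support them:
- A reader might infer that 12-month cases are deleted from the glucose, insulin and HbA1c analyses. The text says only that the person leaves the study. With the intention-to-treat statement beside it, keeping the recorded value is at least as natural a reading.
- A reader might infer that people with diabetes at baseline could be allocated before the confirmatory test and then removed. That rests on silence. The glucose tolerance test is a baseline measure and diabetes is an exclusion criterion, so resolution before allocation is the natural reading.
- A reader might assume 5% v 2% conversion with 2-hour glucose of 12 v 6 mmol/l and conclude that (0.05 - 0.02) × (12 - 6) = 0.18 mmol/l is erased. This charges the whole year's conversions to removal. With a quarter detected by 3 months it becomes about 0.045. The rates also imply a 60% relative reduction in diabetes, which nothing in the protocol supports.

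**Conclusion.** The conflict is real and rests on the protocol's own text: removal after any session and intention-to-treat analysis need to be reconciled for randomised participants. The firm consequence is for 3-month cases, whose 12-month primary and glycaemic outcomes would not be collected. For 12-month cases the defect is an ambiguity about recorded values.

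The loss depends on an outcome, and if the programme works it would tend to bias the glycaemic comparison towards no difference. Its size cannot be established from the protocol. On the assumed 1-5% evenly spread conversion it is about 0.4 to 2.2 people of 178, with a small effect on mainly secondary outcomes and little on the power of the primary. The reason to act is the inconsistency and the irrecoverable data; a large bias has not been shown.

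**What to change.** Reconcile the biochemical variables section with the Phase 3 data analysis section:
- Leave the referral to the general practitioner unchanged.
- Limit removal to diabetes confirmed before randomisation.
- State that a randomised participant with diabetes confirmed later stays in follow-up for the 12-month accelerometry and the other scheduled outcomes. Whether the glucose challenge is repeated is left to the investigators.
- State that such participants are analysed in their allocated arm, that all recorded values are kept (including those from 12 months), and that the diagnosis is recorded.

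The cost is a change of wording and at most a few visits that are already scheduled. The small downside is that glucose values taken after any newly started treatment need a sensitivity analysis. The change should be in place before 3-month sessions begin, because missed 12-month measurements cannot be recreated.

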**Anthropometric and demographic data**

- Blood pressure
- Body weight
- Body fat percentage
- Waist and hip circumference
- Height
- Co-morbidities
- Medications.

Arterial blood pressure will be measured in the sitting position (Omron, Healthcare, Henfield, UK); three measurements will be obtained and the average of the last two measurements will be used. Other measures include body weight and body fat percentage (Tanita BC 420SMA, Tanita, West Drayton, UK), waist circumference (midpoint between the lower costal margin and iliac crest), and height to the nearest 0.1 kg, 0.5% and 0.5 cm respectively. Information on current smoking status, medication history, family history and ethnicity will be obtained by self-report.

### Health related quality of life

### EQ-5D

Health-related quality of life will be measured using the EQ-5D (Kind 1998), which is a standardized questionnaire that was developed for use as a measure of health outcomes and defines health in terms of five dimensions: mobility, self-care, usual activities, pain or discomfort, and anxiety or depression. Data from the EQ-5D can be represented either as a health profile (EQ-5Dprofile) or a health index (EQ-5Dutility) based on time trade-off data from England, which was used to elicit utility weights for the EQ-5D. This instrument can be used to calculate ‘quality adjusted life years’ (QALYs) which are essential to cost-effectiveness analysis.

### Psychological variables and questionnaire data

- Brief Illness Perceptions Questionnaire
- Self-efficacy to increase physical activity and reduce sitting
- Barrier self-efficacy
- Fatigue
- Self-reported measures of sedentary time
- Hospital Anxiety and Depression Score
- Poly cystic ovarian syndrome questionnaire (Pedersen 2007)
- Sleep quality

Several important psychological variables will be measured to establish whether the intervention is targeting the theoretical constructs on which it is based and if so, whether these constructs are determinants of behaviour change as hypothesised.

*Perceptions and perceived knowledge of diabetes risk*

Perceptions and perceived knowledge of diabetes risk will be measured with the validated Brief Illness Perceptions Questionnaire (BIPQ) (Broadbent 2006). This eight item instrument uses an 11 point Likert scale (0 = no effect, 10 = complete effect) to measure five cognitive illness representations (consequences, timeline, personal control, treatment control, and identity), two emotional representations (concern and emotion) and illness comprehensibility (perceived knowledge). The BIPQ provides a practical and comprehensive measurement of determinants identified in Leventhal’s (1980) common sense model, one of the key theoretical models underpinning the content and structure of the education programme. The BIPQ has been shown to have reasonable test-retest reliability and concurrent validity (Broadbent 2006).

*Self-efficacy to increase physical activity and reduce sitting*

Exercise self-efficacy will be measured using the 100% confidence rating scale (from 0% = no confidence to 100% = complete confidence) (Keller 1999). This self-efficacy questionnaire measures participants’ confidence in their ability to undertake any form of moderate- to vigorous-intensity physical activity for 10 minute periods, increasing incrementally from 10 minutes to one hour each day. An overall score is calculated by summing the efficacy scores for each time period and dividing by the number of time periods. Exercise self-efficacy measures using the 100% confidence rating scale have been shown to have good (α > 0.8) internal reliability (McAuley 2003, Cox 2003). To assess self efficacy to reduce sitting time the exercise self-efficacy questionnaire has been modified to focus on confidence to reduce sitting time.

*Barrier self-efficacy*

Participants’ confidence in their ability to self-regulate their exercise behaviour in the face of five commonly identified barriers (tired, bad mood, bad weather, lack of time and holiday) will also be measured (Marcus 1992). This five item questionnaire has been shown to have adequate (α > 0.7) internal reliability (Cox 2003, Marcus 1992). The 100% confidence rating scale will be used; an overall score for self-regulatory efficacy will be calculated by summing the efficacy scores for each barrier divided by the number of barriers.

Fatigue

We will use the Fatigue Scale (Chalder, 1993) to measure fatigue severity. The Fatigue Scale is one of the most widely used measures assessing fatigue and includes 11 items, seven assessing physical fatigue and four assessing mental fatigue. Responses to items are measured using a 4-point Likert-style. A total fatigue score is obtained by adding the score of all 11 items and ranges from 0 (no fatigue) to 33 (maximum fatigue).

*Sedentary time and sleep duration*

We will use a validated questionnaire designed to collect self-report data on time spent in sedentary behaviours (Marshall 2009). We will also devise methods of assessing self-efficacy to reduce sedentary time. Sleep duration has been associated with diabetes risk (Tuomilehto, 2009) and it is feasible that the mediating factor is sedentary behaviour. As such, we will also measure sleep duration and sleep quality via the Pittsburgh Sleep Quality Index (Buysse et al 1989). This is a self-rated questionnaire that assesses sleep quality and disturbances during the previous month.

*Depression and anxiety*

Depression and anxiety will be measured with the 14 item Hospital Anxiety and Depression Scale (Zigmond 2006)

**Dual energy [X-ray](http://www.nhs24.com/content/default.asp?page=s7" \l "x-ray) absorptiometry (DEXA) and** magnetic resonance imaging (MRI) **assessment of body composition**

36 participants (20%) of the STAND study population who are agreeable will be offered imaging to analyse their body fat composition: a whole body dual energy [X-ray](http://www.nhs24.com/content/default.asp?page=s7" \l "x-ray) absorptiometry (DEXA) scan and a single section abdominal magnetic resonance imaging (MRI) scan taken in the L3-L4 region to measure soft tissue body composition, visceral and subcutaneous abdominal fat distribution respectively. As visceral adiposity and overall muscle mass are strongly involved in the aetiology of T2DM these measurements will enable a detailed investigation of the independent effects of sedentary behaviour, physical activity, muscle mass and adiposity in regulating circulating insulin, glucose and adipokines. To our knowledge there are no published data available which investigate the effect of a sedentary behaviour intervention on body composition. Our data may provide preliminary insights into the effect of a reduction of sedentary behaviour on body mass composition. These study measurements will be undertaken in participants who are willing and able to attend University Hospitals of Leicester for these additional tests at each measurement time point. Both scans will be conducted within 14 days of the baseline and follow-up clinical measurement sessions. These scans, by their nature, are unlikely to detect any abnormalities but in the unlikely event that they do our clinical team of doctors will discuss the abnormalities with the participant and their GP, and arrange any further investigations as necessary.

